| ASSESSMENTS                                 |              |            |                               |                      |                      |                               |                                |                                |                                |
| Postpartum urinary retention                       |              |            |                               |                      |                      | X                             |                                |                                |                                |
| Postpartum uterine contraction pain (VAS)          |              |            |                               |                      |                      | X                             | X                              | X                              | X                              |
| Emotion symptoms(EPDS)                             |              |            |                               |                      |                      |                               |                                |                                | X                              |
| Lactation                                          |              |            |                               |                      |                      |                               | X                              | X                              | X                              |

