### **2.3.5.4 Subject drop-out and discontinuation**

- (1) Implementation of rescue due to postpartum hemorrhage, eclampsia, or other obstetric conditions;
- (2) Change of vaginal delivery to cesarean section;
- (3) Infection during delivery;
- (4) Indwelling catheter and the need to use diuretics due to disease within 6 hours after delivery;
- (5) Degree III laceration above the perineal fissure;
- (6) Neonatal transfer after birth;
- (7) The investigator can terminate the subject from continuing the clinical trial at any stage, if the investigator deems that the risks of continuing the clinical trial outweigh the benefits;
- (8) Subject's poor compliance to this trial.

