## 2.8 Outcomes measures

### 2.8.1 Primary outcome

The time point of the first urination after delivery and whether an indwelling catheter was used within 72 hours after delivery will be recorded. In the present trial, postpartum urinary retention is defined as the first urination occurring more than 6.5 hours after delivery and/or if an indwelling catheter is used within 72 hours after delivery.

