## **7. Statistical analysis**

The following is an overview of the statistical considerations. Details of the pre-specified statistical analyses can be found in Statistical Analysis Plan (SAP).

Statistical analysis will be performed by independent analysts by using R (version 4.1.0; R Development Core Team) software. All the analyses will be based on an intention-to-treat principle. Continuous data will be represented by the average, standard deviation, median, minimum and maximum value; categorical data will be represented by the number and percentages. Continuous data will be analyzed using the t test or one-way ANOVA; Wilcoxon-Mann-Whitney test will be used when necessary. Categorical data will be analyzed using the chisquare test or Fisher's exact test. The logistic regression model or linear regression model and linear mixed model will also be used to find the relationship between independent variables. The subgroup relative risk (RR) and the corresponding 95% confidence intervals (CIs) are calculated together with interaction P values.  $P < 0.05$  will be considered statistically significant.

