## 11. Update on the Published Protocol

As compared to the published protocol ([name], [name], Chang Liu, Nicola Robinson, Myeong Soo Lee, Xiaoyang Mio Hu, Hye Won Lee, Rong Zhang, [name]\*. Effectiveness of acupoint hot compress on early puerperal rehabilitation of parturients after natural childbirth: study protocol for a prospective, multi-center, randomized controlled clinical trial. *Clinical and Experimental Obstetrics & Gynecology*.2021;48(6):1350-1357), the present study protocol has made several amendments.

- (1) The medical provision of two centers changed, which has limited the number of the available participants with inclusion criteria of the study, and these two centers were not included in the trial.
- (2) The analysis used in the present trial is referred to as an “per protocol” analysis.
- (3) To detect the effects of acupoint hot compress on reducing the incidence of urinary retention more accurately, we used a broader standard to identify postpartum urinary retention.
- (4) To detect the effects of acupoint hot compress on lactation, we used a detailed measurement to quantify the breastfeeding milk volume.
- (5) As all the outcomes collected from 6±0.5 hours to 76±0.5 hours after delivery, the changes of maternal weight is tiny, so the weight was not included in the analysis.

**Effects of acupoint hot compress during early puerperium on parturients after a vaginal delivery: study protocol for a randomized clinical trial**

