## **1. Study Populations**

All subjects with randomization will be included in the analysis set regardless of whether they receive any treatment. According to the intention-to-treat principle, all analysis will be based on the randomization set.

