## **3. Missing Data**

Missingness is considered to be missing at random (MAR) and multiple imputation (MI) techniques will be used for handling missing data.

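### Drop-out rule (4) overlaps the catheter component of the primary outcome, and the plan does not say how a woman who meets both is analysed

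*Supplement*

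**What the plan says.** **The rule.** Protocol 2.3.5.4, item (4), makes this a ground for drop-out or discontinuation: "Indwelling catheter and the need to use diuretics due to disease within 6 hours after delivery".

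**The outcome.** Protocol 2.8.1 counts a woman as having urinary retention on "first urination occurring more than 6.5 hours after delivery and/or if an indwelling catheter is used within 72 hours after delivery". It also requires the time of first urination and catheter use over the 72 hours to be recorded.

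**Who is analysed.**
- SAP 1: "All subjects with randomization will be included in the analysis set regardless of whether they receive any treatment".
- Protocol 7: "All the analyses will be based on an intention-to-treat principle".
- Protocol 11, item (2): "The analysis used in the present trial is referred to as an “per protocol” analysis". Section 11 lists changes from the published protocol, but this item describes the present trial, so it cannot be set aside as superseded text.

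**Missing data.** SAP 3: "Missingness is considered to be missing at random (MAR) and multiple imputation (MI) techniques will be used for handling missing data".

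**Blinding.** Protocol 2.5 describes an open-label design in which only the outcome assessors and statisticians are blinded.

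**Schedule.** In Figure 1 (Protocol 2.3.3) the row "Postpartum urinary retention" is marked once, at 6±0.5 hours.

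**The concern.** A catheter in the first 6 hours lies inside the 72-hour outcome window. Figure 1 places randomisation at enrolment and allocation at time 0, so it also falls after randomisation. The same observation is therefore both an event and a reason to leave the trial, and the documents do not say which takes precedence.

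If leaving the trial takes precedence, inclusion in the primary comparison depends on the outcome. Staff who know the arm would normally decide whether to place a catheter and whether to invoke the rule, so removal could differ between arms. What is at stake is the validity of the primary RR, and a larger sample does not cure a bias of this kind.

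**Working it through.** **Step 1: does the overlap depend on how rule (4) is read?** The wording allows three readings.

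| Reading of rule (4) | Woman removed because of a catheter | Meets 2.8.1? |
|---|---|---|
| Two separate grounds, with disease qualifying only the diuretics | Any indwelling catheter by 6 h | Yes |
| Two separate grounds, both disease-related | Catheter placed for disease by 6 h | Yes |
| Both conditions together | Catheter plus diuretics, for disease, by 6 h | Yes |

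The reading changes how many women are affected, not whether there is a conflict, because 2.8.1 carries no exception for cause or timing.

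**Step 2: what happens to her in the analysis?**
- Per protocol (Protocol 11, item 2): she would be dropped and her event lost.
- Intention to treat (Protocol 7, SAP 1): she stays in the set. No sentence says she is scored as an event or that outcome recording continues after drop-out. If her outcome were treated as missing, SAP 3 would impute it under MAR although it is known.

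**Step 3: possible size.** The pilot risks in Protocol 2.4 are 7.7% (intervention) and 25.7% (control), so RR = 0.077/0.257 = 0.30 and the risk difference is 18.0 points. The planned 600 per group less 20% drop-out leaves 480. The share f of events that rule (4) would remove is not given; 10%, 25% and 50% are assumptions.

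If a share f of events is removed from an arm with risk p, the remaining risk is p(1−f)/(1−pf). At f = 50% this is 0.0385/0.9615 = 4.0% (intervention) and 0.1285/0.8715 = 14.7% (control).

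*Same share removed in both arms:*

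| f | Intervention | Control | RR | Difference (points) | Events removed per 480 (intervention / control) |
|---|---|---|---|---|---|
| 0 | 7.7% | 25.7% | 0.300 | 18.0 | 0 / 0 |
| 10% | 7.0% | 23.7% | 0.294 | 16.8 | 3.7 / 12.3 |
| 25% | 5.9% | 20.6% | 0.286 | 14.7 | 9.2 / 30.8 |
| 50% | 4.0% | 14.7% | 0.272 | 10.7 | 18.5 / 61.7 |

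Power (one-sided 0.025) stays above 99.9% in every row.

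*Different shares, pilot risks:* removing 25% of intervention and 50% of control events gives RR = 0.0589/0.1474 = 0.40. Removing 50% and 25% gives 0.0400/0.2060 = 0.19. The RR before removal is 0.30.

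*Different shares, no true effect (25.7% in both arms):* removing 50% of intervention and 25% of control events gives RR = 0.1474/0.2060 = 0.72. The reverse gives 0.2060/0.1474 = 1.40. In the first case 480×(1−0.1285) = 418 and 480×(1−0.06425) = 449 women remain. The standard error of the difference is √(0.1474×0.8526/418 + 0.2060×0.7940/449) = 0.0258, so the expected z is 0.0585/0.0258 = 2.27. The probability of z above 1.96 in favour of the intervention is then about 62%, where 2.5% is intended.

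**Step 4: Figure 1.** The only marked retention assessment ends at 6.5 hours. The definition needs more than 6.5 hours, or a catheter at any time up to 72 hours, so that visit alone cannot establish the outcome.

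**The case against.** **The rule looks narrow.** It joins the catheter to diuretics and to disease, and it stands among obstetric complications such as haemorrhage, eclampsia and infection. A fair reader may conclude that it is meant for medically complicated cases and leaves ordinary retention catheters alone. That stands as a limit on scope, and the number affected may be small. It does not remove the conflict, because 2.8.1 still counts those catheters.

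**Events may never be lost.** A reader might infer that the trial discards its own events. The documents do not establish that. Protocol 7 and SAP 1 keep every randomised woman, 2.3.5.4 does not say that drop-out means leaving the analysis, and 2.8.1 requires catheter use to be recorded. Nor does SAP 3 say that a recorded catheter is set to missing. Loss follows only from the per-protocol statement or from stopping data collection at drop-out; imputation follows only if the outcome is treated as missing. What remains is that nothing in the plan protects these events.

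**Power is not threatened on the plan's own risks.** One can construct a collapse in power by assuming that the compress prevents only early catheters, but that replaces the stated 7.7% with a much higher intervention risk. On the pilot risks with equal removal, power stays above 99.9%. The issue is bias.

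**Figure 1 is a small point.** 2.8.1 already requires recording to 72 hours, so the single mark does not show that data go uncollected.

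**Timing against treatment.** Intervention I starts within 30 minutes of delivery (Protocol 2.6.2), so a catheter could come before it. The argument needs only that the catheter follows randomisation.

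**Conclusion.** The point holds as a conflict between sections with unstated handling. Rule (4) overlaps a component of the primary outcome on every reading. The per-protocol statement would lose those events; the intention-to-treat statements keep the women but do not say how they are scored.

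The size cannot be derived from the documents. If removal is equal across arms, the RR barely moves (0.30 to between 0.29 and 0.27), although the risk difference falls from 18.0 to as little as 10.7 points. If removal differs by arm, the bias can go either way: with no true effect, shares of 50% and 25% give an RR of 0.72, or 1.40 when reversed. These shares are illustrations, and nothing in the documents shows that removal will be this large or this unequal. The point still needs correcting before analysis, because it decides who counts as a primary event.

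**What to change.** 1. Reconcile Protocol 2.3.5.4 item (4), 2.8.1, 7 and 11 item (2) with SAP 1. State that meeting rule (4) does not remove a randomised woman from outcome follow-up or from the primary analysis, and that her observed outcome is scored under 2.8.1.
2. State in SAP 3 that observed events are never set to missing and imputed.
3. Reword rule (4) so that all centres read it alike.
4. If catheters placed for another medical reason are to be treated differently, define that within the outcome, adjudicate it blind to arm, and report a sensitivity analysis that handles them the other way.
5. As a minor alignment, make Figure 1 match the 72-hour recording that 2.8.1 already requires.

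The cost is protocol and SAP wording, schedule marks and one sensitivity analysis, plus blinded adjudication if the exception in item 4 is adopted. No extra participants are needed. No position is taken on the use of catheters or diuretics, or on stopping study treatment.

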## **2.4 Sample size calculation**

This study will use a superiority design. According to the pilot study, the incidence rate of urinary retention was 7.7% in the intervention group and 25.7% in the control group. Assuming a 1 : 1 ratio of intervention to control group and using a one-sided test, a significance level ( $\alpha$ ) of 0.025 and a power ( $1-\beta$ ) of 80% and a possible drop-out rate of 20%, the estimated sample size is 600 cases in each group with 50 cases at each center in each group. Intervention and control groups would require a total sample size of 1200 cases.

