**Figure 2. Trial flow chart**

## 2.3.4 Recruitment

The study will be conducted in 12 hospitals in China: Women's Hospital, School of Medicine, Zhejiang University; Tongde Hospital of Zhejiang Province; Yiwu Maternity and Child Health Care Hospital; Jiaxing Maternity and Child Health Care Hospital; Zhejiang Xiaoshan Hospital; Zhoushan Women and Children Hospital; Shaoxing Maternity and Child Health Care Hospital; The Women & Children Hospital of Dongyang; Ruian People's Hospital; Cixi Maternity and Child Health Care Hospital; Wenling Maternity and Child Health Care Hospital and Xianju People's Hospital. Posters will be placed in each institution's bulletin board to recruit subjects. No specific culture, race, or socio-economic group will be targeted or restricted from the recruitment.

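### The 600 per group in protocol 2.4 does not follow from the inputs given for it, which need about 80 to 97 per group including drop-out

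*Supplement*

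**What the plan says.** Protocol 2.4 sets out one calculation for the primary outcome, postpartum urinary retention. It opens with "This study will use a superiority design" and takes its rates from a pilot study, in which "the incidence rate of urinary retention was 7.7% in the intervention group and 25.7% in the control group". The other inputs are equal allocation, a one-sided test at 0.025, 80% power and a possible drop-out of 20%. The same sentence then gives the result: "the estimated sample size is 600 cases in each group with 50 cases at each center in each group". The total is stated as 1200.

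The figure of 50 per centre per arm matches protocol 2.3.4, which says "The study will be conducted in 12 hospitals in China". Protocol section 11, which lists changes from the published protocol, says of two centres whose medical provision changed that "these two centers were not included in the trial".

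Three other places bear on the calculation. Protocol 2.5 randomizes individual subjects. SAP 2 tests at a two-sided 5% level. SAP 5 compares the groups by unadjusted logistic regression and reports a relative risk with a 95% confidence interval. Neither document states a superiority margin, a design effect, an intracluster correlation, or a secondary, subgroup or safety aim that determined the size.

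**The concern.** Section 2.4 presents 600 as what its inputs produce. A fall from 25.7% to 7.7% is large, 18 percentage points, and a difference of that size needs far fewer than 600 per group at 80% power. Either an input has been misreported or 600 was reached in some other way that the protocol does not record.

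What is at stake is how the trial is read. The sample-size paragraph tells the reader which effect the trial was built to detect. Anyone who takes 2.4 at face value will think the trial was sized for an 18-point reduction with a one-in-five chance of missing it. At the stated size it is sensitive to much smaller reductions, and the reader cannot tell whether such a reduction was ever the target.

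**Working it through.** **Inputs, all from protocol 2.4.** Intervention rate p1 = 0.077; control rate p2 = 0.257; difference d = 0.180; 1:1 allocation; one-sided 0.025, so z = 1.960; 80% power, so z = 0.8416; drop-out 20%. The margin is taken as zero because none is stated. The two-sided 5% level in SAP 2 uses the same critical value, so it changes nothing.

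**The plan's own figure.** 12 centres × 50 = 600 per group, and 2 × 600 = 1200. The centre arithmetic reproduces the figure. The power calculation does not:

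- Unpooled variance: n = (1.960 + 0.8416)² × (0.077 × 0.923 + 0.257 × 0.743) / 0.180² = 7.849 × 0.26202 / 0.0324 = 63.5, so 64.
- Pooled variance, mean rate 0.167: n = [1.960 × √(2 × 0.167 × 0.833) + 0.8416 × √0.26202]² / 0.0324 = (1.0338 + 0.4308)² / 0.0324 = 66.2, so 67.
- Continuity-corrected: n = (66.2 / 4) × [1 + √(1 + 4 / (66.2 × 0.180))]² = 76.9, so 77.

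**With drop-out, n / 0.8.**

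| Method | Before drop-out | After drop-out | 600 divided by this |
|---|---|---|---|
| Unpooled | 64 | 80 | 7.5 |
| Pooled | 67 | 84 | 7.1 |
| Continuity-corrected | 77 | 97 | 6.2 |

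The arcsine formula gives 63 (79 with drop-out). Power for Fisher's exact test passes 80% at about 73 to 74 per group (about 92 to 93 with drop-out).

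**Could other conventions give 600?** Levels of one-sided 0.05, two-sided 0.05 and two-sided 0.025 were tried, each with 80%, 90% and 95% power, with and without continuity correction. The largest result, at two-sided 0.025, 95% power and continuity correction, is 173 per group including drop-out.

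**Could an unstated feature give 600?** Removing 20% leaves 600 × 0.8 = 480 evaluable per group.

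- Each centre powered separately: no. One centre with 50 per arm has 68% power, and with 40 evaluable it has 58%.
- Clustering: this would need a design effect between 480 / 77 = 6.2 and 480 / 67 = 7.2. Subjects are randomized individually and the primary model has no centre term.
- Superiority margin m: solving 7.849 × 0.26202 / (0.180 − m)² = 480 gives 0.180 − m = 0.0655, so m is about 11.5 points. This value is obtained only by working back from 600.

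**What the stated size delivers.** Power for 7.7% against 25.7% with 480 per group is Φ[(0.180 × √480 − 1.0338) / 0.5119] = Φ(5.68), above 99.99%. Against a control rate of 25.7%, 80% power is reached at an intervention rate of about 18.2% (difference 7.5 points, relative risk 0.71). If all 600 per group contribute, it is reached at about 19.0% (6.7 points, relative risk 0.74).

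**The case against.** The best defence is that the discrepancy does no inferential harm. The trial is larger than its inputs require, the type I error is unaffected, and the primary test does not change. SAP 5 reports a relative risk with its interval, so the size of any effect will be visible whatever the planning text says. All of this stands, and it confines the point to justification and transparency. It does not make 600 the result of the calculation that 2.4 presents.

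A reader might go further in four ways that the documents do not support.

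- *The trial is underpowered.* It is not: power for the stated rates exceeds 99.99%.
- *The stated power and the stated effect contradict each other.* Planned power is usually read as a minimum, and a trial with more than 99.99% power meets an 80% minimum. What fails is the step from inputs to figure.
- *A margin was used, so SAP 5 tests the wrong hypothesis.* No margin appears anywhere. The 11.5 points is back-solved, and SAP 5 describes an ordinary comparison. This is a question for the sponsor and no demonstrated defect.
- *The true size is 500 per arm.* Section 11 is a summary of changes from a published protocol whose centre count is not given here. It does not say whether the 12 hospitals in 2.3.4 are counted before or after the removal, and 12 × 50 agrees with 2.4. Taking 10 × 50 = 500 assumes that the 12 are counted before removal and that the quota stayed fixed. Even then, 500 × 0.8 = 400 evaluable per group would keep power above 99.99%, so the point does not depend on it.

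**Conclusion.** The point holds as an error in the written justification. The inputs in 2.4 require 80 to 97 per group including drop-out; 600 is 6.2 to 7.5 times that, and neither document supplies a reason for the difference. No conventional choice of formula, sidedness or power closes the gap.

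The conclusion rests on a zero margin and on individual randomization without cluster inflation, which is how both documents read. The detectable effect of 7.5 points further assumes that the control rate is 25.7% and that the full planned 20% is lost.

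The documents do not show which element is wrong. An input may have been misreported, or 50 per centre per arm may have been fixed on grounds that were not written down. Only the sponsor can say.

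**What to change.** Restate protocol 2.4 so that the figure and the inputs agree, by one of two routes.

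1. If an input was misreported, correct it and show that the corrected set gives 600.
2. If the inputs are right, say that they need about 67 per group (84 with 20% drop-out) and give the actual basis for 50 per centre per arm. Report the effect detectable at 80% power at the stated size: about 18.2% against 25.7% with 480 evaluable per group. Label this as computed afterwards. SAP 9 records that available data had already been examined, so an undated figure could be mistaken for the planning target.

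If a superiority margin was in fact used, state it in 2.4 and align the primary comparison in SAP 5 with it.

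Also say whether the 12 centres and 1200 subjects are counted before or after the removal described in section 11, and give the centre count and total on one basis.

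The cost is one paragraph of protocol text and a less tidy sample-size rationale. Enrolment does not change. SAP 5 changes only if a margin is confirmed.
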